**Continuous hemofiltration during extracorporeal circulation**

**1.- Abstract**

Perfusionists are healthcare professionals with a university degree whose work consists of providing the necessary medical care to maintain and control an adequate blood flow rate in patients who undergo cardiovascular surgery in which is necessary to fully or partially replace cardiac and/or pulmonary function in any medical-surgical procedure involving Cardiopulmonary Bypass (CPB).

Morbidity during heart surgery with CPB is largely due to physiological problems resulting from the blood coming into contact with foreign surfaces such as cannulas, tubing and especially the membrane oxygenator, leading to a condition known as Systemic Inflammatory Response Syndrome (SIRS), as well as hyperlactatemia (HL) caused by hemodilution, tissue hypoxia, low flows during CPB and hyperglycemia, among other factors.

**2.- Purpose**

The purpose of the research is to determine whether, by controlling the patient's hemodilution level and, therefore, the acute anemia caused by the CPB priming fluid, continuous conventional ultrafiltration (CUF) can decrease serum lactate levels during normothermic CPB by increasing the hematocrit and, consequently, the supply of oxygen to the tissues, and whether the hemofiltration membrane can remove lactate molecules in situations of HL in CPB.

This will be done by performing arterial and venous blood gas analyses every 20 minutes during CPB to measure blood lactate levels, pH, oxygen delivery (DO2), oxygen consumption (VO2), oxygen extraction (ERO2), venous oxygen saturation (SvO2), arterial and venous carbon dioxide difference (△pCO2) and lactate levels in the effluent from the hemoconcentrator.

The perfusionist's role is essential during the procedure, as they control both Cardiac Output (CO) and gas exchange, as well as a number of variables that, depending on their action, will affect blood lactate levels.

**3.- Background and current state of affairs**

Since [name] [1] performed the first heart surgery with cardiopulmonary bypass (CPB) in 1952 to the present day, important technological advances have been achieved, which have made this an increasingly safe technique to use during surgery.

According to the records of the Spanish Society for Thoracic-Cardiovascular Surgery [2], 33,204 procedures were performed in 2013, of which 45.48% were performed with CPB.

CPB is the procedure that supplies oxygenated blood to the systemic circulation while the lungs and the heart remain stopped so that the cardiovascular surgeon can perform various surgical procedures that it would otherwise be impossible to carry out, such as valve replacements and aortic repair, septal defect repair, coronary artery bypass graft, etc.

Before starting CPB a system of cannulas is required to drain the blood from the heart and return it, once oxygenated, to the most suitable artery for its reinfusion in the systemic circulation.

Cannulation of the ascending aorta is the surgeon's first choice and it is necessary to find the healthiest segment in order to avoid cerebral embolism in patients with atheromatous plaques. Other arteries into which the oxygenated blood can be infused are the femoral artery, the subclavian artery and the axillary artery, which are chosen when perfusion via the ascending aorta is not possible due to lesions (aneurysm, dissection) or surgical reinterventions with CPB.

The patient's venous blood is drained by cannulation of the vena cava and right atrium or selective cannulation of the superior and inferior vena cava or the femoral vein. The choice of drainage system depends on the patient's condition.

The venous blood drains into the circuit via polyvinyl chloride (PVC) tubes. From there, once filtered and defoamed, it passes into a polycarbonate reservoir that uses a roller or centrifugal pump to propel the blood to a thin microporous polypropylene hollow fibre membrane that is composed of two phases: a blood phase and a gas phase, which mimic the capillaries of the lungs. This membrane is folded inside a polycarbonate case in such way that it provides a large contact surface area for gas exchange, the operation of which is based on Fick's law of diffusion, which establishes that the rate of diffusion is proportional to the partial pressure gradient of the gas in the direction of diffusion.

Correct cannulation of the patient before starting CPB, as well as the choice of the cardiopulmonary priming solution, allows us to perform the procedure safely, ensuring proper perfusion of the patient's organs and tissues.

Once CPB begins, the tissues are artificially perfused, for which the perfusion pump must be adjusted to a flow rate that is equal to the cardiac output of a healthy adult [3] (2.5 l/min/m2). This rate is adjusted throughout the CPB procedure to adapt to the patient's metabolic needs in order to ensure aerobic metabolism of the different organs and tissues, as the acute hemodilution caused by the priming liquid reduces the blood's oxygen content and blood viscosity, consequently causing hypotension.

Traditionally, during CPB, perfusionist nurses managed a series of gasometric, hematic and electrolyte values that, in theory, ensured safe extracorporeal perfusion, correcting them according to the flow of the CPB pump and temperature in order to maintain normal blood pH between 7.35 and 7.45, venous oxygen saturation (SvO2) >65 mmHg to ensure tissue perfusion, a hematocrit above 22% so as not to decrease the availability of oxygen in the blood, and blood glucose, calcium, sodium and potassium values within the normality.

HL can occur during or after CPB without clinical signs of hypoxia [4], increasing postoperative complications such as renal insufficiency (RI), neurological and respiratory changes and hemodynamic instability and causing acidosis. Consequently, patients require more time on mechanical ventilation, are hemodynamically unstable and more vulnerable to infections, all of which lengthens the patient's stay in the intensive care unit (ICU) and can lead to death [5].

Lactic acid is produced from pyruvic acid in a reaction catalyzed by lactate dehydrogenase and is rapidly buffered by the extracellular bicarbonate to produce lactate, normal serum values of which are lower than 2 mmol/L.

HL can begin according to organ involvement and is classified by whether it is related (type A) or unrelated (type B) to tissue hypoxia [6].

Type A HL is associated with CPB due to acute hemodilution and a deficient oxygen supply [7, 8] and is linked to patient morbidity and mortality in the postoperative period when lactate levels are above 4 mmol/L during the surgical procedure [9], as well as prolonging patients' stay in the Intensive Care Unit (ICU).

Intraoperative HL in heart surgery is observed in between 10% and 21% of patients once CPB begins, persisting until the patient reaches the ICU, and it is related to a higher rate of postoperative complications and mortality.

By correcting the risk factors that cause HL during CPB it is possible to control this metabolic disorder and improve patients' prognostic.

In the Perfusion Unit of the Cardiovascular Surgery Unit of Hospital Universitario Puerta del Mar in Cádiz, surgery with CPB that does not require circulatory arrest is performed under normothermic conditions using an alpha-stat acid-base management strategy, as there is no need to correct the pH values based on the temperature. Similarly, the central venous saturation values (SvO2) as an indication of the ratio between oxygen consumption and oxygen supply in relation to the patient's body surface area (DO2i), oxygen extraction (ERO2) and difference between carbon dioxide tension in arterial and venous blood (△pCO2) will be recorded every 20 minutes.

The △pCO2 is a very important value that helps the perfusionist detect capillary hypoperfusion in surgical patients during CPB, as a difference in arterial and venous pCO2 above 8 mmHg, even with optimum SvO2 values of >70%, is related to an increase in intraoperative lactate and a decrease in splanchnic function [10].

But there are intraoperative situations in which HL cannot be controlled during CPB, as is the case of patients with hepatic failure, renal failure, intraoperative blood transfusions and pre-surgical HL. In these patients, the evolution of HL is made worse by longer duration of CPB and hypotension during the procedure [11].

Hemofiltration is performed at two clearly distinct points during heart surgery. During CPB it is called conventional ultrafiltration (CUF) and it depends directly on the content of the venous reservoir in the CPB circuit. Modified ultrafiltration (MUF) is independent of this circuit and is performed once the CPB procedure is finished. Both use a highly permeable polysulfone hollow fibre filter housed in a polyvinyl chloride (PVC) cylinder. A pressure gradient and concentration are used to extract liquids, electrolytes and non-protein-bound solutes with a molecular weight below 50,000 Daltons.

Traditionally, CUF is performed in patients with acute kidney injury (AKI), fluid overload (CPB pump priming fluid, cardioplegic solution) and intraoperative hyperkalemia.

MUF seeks to achieve more effective hemofiltration by hemoconcentrating the patient and reducing inflammatory mediators [12].

The surgical team at Puerta del Mar University Hospital who are taking part in the research usually use a polysulfone membrane throughout the procedure and perform high-flow continuous ultrafiltration (UF), replacing the filtered volume with Prismasol 2® pharmaceutical solution, which contains the following active substances: calcium chloride, dihydrate; magnesium chloride, hexahydrate; glucose monohydrate, lactic acid solution 90%; sodium chloride; potassium chloride and sodium hydrogen carbonate. This solution is also used for priming the CPB circuit, and it must be taken into account in the research that Prismasol 2® solution contains 3 mEq/L of lactate.

Prismasol 2® solution is used as a solution for hemofiltration in the treatment of renal insufficiency and no contraindications with CPB have been reported, since serum potassium and calcium levels are monitored every 20 minutes. The administration of sodium bicarbonate is also eliminated from priming.

Likewise, CUF during CPB is safe thanks to continuous patient monitoring throughout the procedure.

The flow rates recommended by the manufacturer for the replacement solution in hemofiltration and hemodiafiltration are as follows: Adults and adolescents: 500 - 3000 ml/hour.

The use of hemofiltration in adults during CPB procedures has evolved over the years, with studies showing the advantages of CUF or MUF in CPB procedures, such as increased hematocrit with the consequent reduction in blood transfusions, reduction of inflammatory response, improvement of hemodynamic parameters and better neurological outcomes in patients, as well as a shorter postoperative intubation time in the intensive care unit [13].

There is a disparity in the scientific literature regarding HL during and after CPB, and while Soliman R et al. [14] consider that continuous hemofiltration increases postoperative lactate levels and inotropic drug use, Kiziltepe et al. [15] describe it as a safe procedure in adult patients undergoing cardiac surgery.

Perhaps the results of the Soliman group were conditioned by the use of moderately hypothermic CPB and the use of Ringer's lactate solution at a concentration of 27.8 mEq/L for priming the CPB circuit.

In terms of blood purification strategies in cardiac surgery, the debate focuses currently on finding out which hemofiltration method is most appropriate: CUF, MUF or a combination of the two strategies. In children, a combination of both therapies seems to be the most effective strategy [16].

In the Cardiovascular Surgery Unit of Puerta del Mar University Hospital, CUF is the technique performed during CPB. The oxygenator propels the blood into the aortic cannula through a 3/8 tube and through a smaller cannula with a 1/16 diameter into the hemofilter. The flow needed from the oxygenator to maintain an intravascular perfusion pressure in the patient depends on changes in systemic vascular resistance. Thus, in the venous reservoir prior to the oxygenator, the volume of blood recovered to be oxygenated from the cannulas may be lower in the event of systemic vasodilation. This is because the anterograde flow (l/min) in the CPB circuit has to be increased to maintain a constant perfusion pressure. By managing the resistance in the efferent line of the filter, transmembrane pressure is increased. This makes it possible to achieve sufficient ultrafiltration through the high-permeability membrane in a controlled manner, even when the blood flow from the oxygenator is not very high. The replacement fluid is administered into the venous reservoir prior to the blood oxygenator. Thus, the resulting hemodilution can be controlled by serial intraoperative controls, maintaining hematocrit values of about 25%. The goal is to achieve a net balance of zero, although it may vary depending on extra hemodilution due to perfusions and intravenous fluid therapy by the anesthetist. Finally, the volume in the lines and the reservoir undergoes an independent hemoconcentration process without prolonging the surgical procedure, once the patient is decannulated, obtaining a bag of packed red blood cells with a hematocrit of 60%. This method benefits from the advantages of the MUF over CUF without any of its disadvantages, such as delaying the completion of surgery.

Taking into account our experience, normothermic CPB allows much more effective oxygen extraction from the tissues than hypothermic CPB, especially splanchnic tissue, reducing bacterial translocation due to hypoperfusion, improving perfusion and avoiding anaerobic metabolism in distal vascular beds.

We will also analyze the possible beneficial effects of optimal therapy on clinical progress in the ICU in the form of reduced need for blood transfusion, mechanical ventilation for less than 24 hours, reduced need for extracorporeal renal support, reduced need for vasoactive drugs, shorter stay in the ICU, shorter hospital stay and reduced mortality. This analysis will enable us to collect information that will allow subsequent patient follow-up in terms of morbidity and mortality.

Finally, based on the important role of perfusion nursing care in patients undergoing cardiac surgery with CPB, and in view of the lack of scientific production in this respect, we propose to assess patients who undergo CPB by means of NANDA, NIC and NOC nursing terms before and after surgery. There are other taxonomies, but these are the most widely accepted and will be used as follows:

- NANDA diagnosis (North American Nursing Diagnosis Association).
- NOC (Nursing Outcomes Classification) of the patient’s current situation and the outcome we hope to achieve.
- NIC (Nursing Interventions Classification).
- NOC that we have achieved.

The interrelationship between these three taxonomies [17] describes the actual or potential problem that we have detected in the patient and the aspects of that problem that we are attempting or hope to solve with one or more nursing interventions, in which one or more activities needed to solve the problem will also be used.

Diagnoses:

- NANDA Code 0027: “Fluid Volume Deficit”
  - Definition: Decreased intravascular, interstitial and/or intracellular fluid. This refers to dehydration, water alone without changes in sodium.
    - NOC Code 0601:
      - Definition: “Water balance in the intracellular and extracellular compartments of the body”.
        - NIC 4120 “Fluid management”: Promotion of fluid balance and prevention of complications resulting from abnormal or undesired fluid levels.
        - NIC Code 4130: “Fluid Monitoring”: Collection and analysis of patient data to regulate fluid balance.
        - NIC Code 7690: “Laboratory data interpretation”: Critical analysis of patient laboratory data in order to assist with clinical decision making.
        - NIC Code 4180: “Expansion of intravascular fluid volume in a patient who is volume depleted”
- NANDA Code 00016: “Impaired urinary elimination”
  - Definition: Impaired urinary elimination.
    - NOC Code 0503:
      - Definition: “Collection and discharge of urine”.
        - NIC Code 0590: “Urinary elimination management”: “Maintenance of an optimal urinary elimination pattern”.
        - NIC Code 2300: “Preparing, giving and evaluating the effectiveness of prescription and nonprescription drugs”
        - NIC Code 1876: “Management of a patient with urinary drainage equipment”
        - NIC Code 4120: “Fluid management” Promotion of fluid balance and prevention of complications resulting from abnormal or undesired fluid levels.
- NANDA Code 00030: “Impaired gas exchange”
  - Definition: Excess or deficit in oxygenation and/or carbon dioxide elimination at the alveolar-capillary membrane.
    - NOC Code 3350:
      - Definition: Adequacy of blood flow through pulmonary vasculature to perfuse alveoli/capillary unit.
        - NIC Code 3350: “Respiratory monitoring”: Collection and analysis of patient data to ensure airway patency and adequate gas exchange.
        - NIC Code 7690: “Laboratory data interpretation”: Critical analysis of patient laboratory data in order to assist with clinical decision making.
        - NIC Code 6680: “Vital signs monitoring”.
        - NIC Code 3320: “Oxygen therapy”.
- NANDA Code 00029: “Decreased cardiac output”.
  - Definition: “Inadequate blood pumped by the heart to meet the metabolic demands of the body”
    - NOC Code 0401
      - Definition: Unobstructed, unidirectional blood flow at an appropriate pressure through large vessels of the systemic and pulmonary circuits.
        - NIC Code 4064: Circulatory care: mechanical assist device.
        - NIC Code 4030: Blood products administration.
        - NIC Code 7690: “Laboratory data interpretation”: Critical analysis of patient laboratory data in order to assist with clinical decision making.
        - NIC Code 4130: “Fluid Monitoring”: Collection and analysis of patient data to regulate fluid balance.
        - NIC Code 6680: “Vital signs monitoring”
        - NIC Code 4210: “Invasive hemodynamic monitoring”
        - NIC Code 4150: “Hemodynamic regulation”
        - NIC Code 6650: “Surveillance”

**4.- Hypothesis and Objectives**

**4.1.- Rationale:**

The intraoperative use of hemofiltration in cardiac surgery in adults has evolved from its initial indication for renal, metabolic and volume control to an immunomodulatory intention as more pathophysiological knowledge has been gained about the process.

In adults, the benefits of using ultrafiltration versus not doing so are clear, although its use is not very widespread, especially in the case of modified ultrafiltration, with disparate published results and conclusions regarding the degree of immunomodulation that hemofiltration produces and its impact on clinical outcomes.

This work aims to study the impact of using polysulfone membranes on continuous ultrafiltration with volume replacement in patients undergoing cardiac surgery. In this type of surgery, techniques such as conventional ultrafiltration (CUF) and modified ultrafiltration (MUF) are known for controlling the patient's fluid balance during the procedure. However, there is no scientific evidence on the benefits of continuous hemofiltration with volume replacement and its effect on lactatemia.

**4.2.- Hypothesis:**

- Continuous ultrafiltration with volume replacement using a polysulfone membrane during CPB in patients undergoing cardiac surgery decreases intraoperative lactatemia.
- Patients undergoing cardiac surgery and continuous ultrafiltration with volume replacement using a polysulfone membrane have a lower postoperative morbidity and mortality rate than patients undergoing cardiac surgery without hemofiltration.
- Patients undergoing cardiac surgery and continuous ultrafiltration with volume replacement using a polysulfone membrane have a better health status after surgery than patients undergoing cardiac surgery without hemofiltration. (Assessed by NNN taxonomies: NANDA, NOC, NIC).

**4.3.- General objectives:**

- To determine whether continuous ultrafiltration with volume replacement using a polysulfone membrane during CPB in patients undergoing cardiac surgery decreases intraoperative lactatemia.
- To assess morbidity and mortality with the use of CPB and continuous hemofiltration.
- To evaluate the health status of patients before and after surgery with CPB using the NNN taxonomies (NANDA, NOC, NIC).

**4.4.- Specific objectives:**

- To determine plasma lactate levels in patients who undergo CPB at different stages of the process:
  - 10 minutes after starting CPB.
  - Every twenty minutes until the end of the CPB procedure
  - Twenty minutes after stopping CPB.
- To determine lactate levels in the effluent.
- To describe the behavior of variables that may influence intraoperative lactatemia levels.
- To evaluate the effects of using the polysulfone membrane continuously during the intraoperative and postoperative period.
- To describe the epidemiological profile, risk factors and surgical risk, according to the usual scores, of the patients in the study.
- To analyze the complications and side effects deriving from CPB and continuous hemofiltration with volume replacement.
- To identify patients' health status using the NANDA diagnosis classification.
- To assess patients' status of using the Nursing Outcomes Classification (NOC), before and after surgery with CPB.
- To evaluate the efficacy of the Nursing Interventions Classification (NIC), after CPB surgery using the Nursing Outcomes Classification (NOC).

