**5.- Methodology**

**5.1.- Study design**

A randomized, patient- and data analyst-blinded clinical trial to compare outcomes in terms of the lactate clearance rates (quantity/unit of time) of the assigned therapy groups. Two treatment groups will be established: one control group without hemofiltration (CG or 1), one group with hemofiltration using a polysulfone filter (PG or 2).

To ensure an unbiased assessment of treatments, randomization will be performed in eight blocks of five patients. The study groups will be equivalent in all aspects except the procedures they undergo.

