**5.4.- Description of methods:**

The proposed methods to be used in this study are based on analyses of the following instruments and variables:

- Clinical and analytical instruments.
- Record sheet of variables from the patient's medical record.
- Record sheet of intraoperative variables.
- Graph from the perfusionist and electronic data collection systems.
- Record sheet of postoperative variables.
  - Graph and records from the ICU.
  - Graph and records from the ward.
  - Lactate testing instruments.

The variables to be studied have been selected according to the existing literature regarding the factors associated with the results of the therapy used.

- Dependent variables:
  - Levels of serum lactate in mmol/L (continuous quantitative variable): at the beginning of CPB, after 10 minutes of CPB, every 20 minutes during the procedure and 20 minutes after the end of CPB.
  - Effluent lactate levels in mmol/L (continuous quantitative variable): at the end of the procedure.
  - Intra- or perioperative mortality, yes/no (dichotomous variable).
  - Complications: intubation, seizures, pleural effusion requiring drainage, yes/no (dichotomous variable).
  - Evaluation of the outcome of the intervention by the perfusionist nurse. During CPB. NOC nursing taxonomy in the preoperative period, at the end of each procedure and in the postoperative period. These outcomes consist of indicators that measure the patient's health on a Likert scale (1-5).
- Adjustment or stratification variables:
  - Predicted mortality scale (EuroSCORE[[1]](#footnote-2)).
  - Serum potassium and lactate values, immediately after surgery and with each routine blood analysis in the ICU.
- Preoperative variables:
  - Demographic variables:
    - Age: years (quantitative variable).
    - Sex: male/female (dichotomous variable).
- Biometric variables:
  - Height: centimeters (continuous variable).
  - Weight: kilograms (continuous variable).
    - The above variables will be used to calculate the body mass index (BMI): weight/height2 = kilograms/m2 (continuous variable).
- Biochemical variables:
  - Glucose: mg/dL (continuous variable).
  - Serum lactate: mmol/L (continuous variable).
  - Diagnosis upon admission: according to ICD-9 international classification.
    - Comorbidities: presence/absence in the patient's medical record (dichotomous variables):
      - Arterial hypertension.
      - Hyperlipidemia.
      - Peripheral artery disease.

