**5.7.- Statistical analysis [24]:**

- Descriptive analysis of variables: measures of central tendency and dispersion will be shown in the case of quantitative variables, while frequencies and proportions will be shown in the case of categorical variables.
- The normality of the variables will be checked using graphs and the Kolmogorov-Smirnov test.
- Homogeneity and comparability between the groups of the two arms of the study in the main confounding factors considered will be verified at the beginning of the study by means of a comparison of proportions (chi-squared test or Fisher's exact test, if necessary) and a comparison of means (Student's t-test and the Mann-Whitney U test in case of non-parametric distributions).
- The intrasubject change over time will be analyzed by comparing paired means using a t-test or Wilcoxon signed rank test (non-parametric variables), quantifying the change in each measure in relation to the baseline reference measure (first sample).
- The bivariate analysis between the CG and PG will be performed using the chi-squared test or Fisher's exact test, if necessary, and using a comparison of means (Student's t-test and Mann-Whitney U test in case of non-parametric distributions).
- In the event of non-homogeneity in any variable between the groups studied, a multivariate analysis will be performed using linear regression.

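### Section 4.4 sets out to evaluate the efficacy of the nursing interventions (NIC), but the design has no comparator for them, so change in NOC scores can neither show nor rule out an effect

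*Protocol*

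**What the plan says.** The last specific objective in Protocol section 4.4 is "To evaluate the efficacy of the Nursing Interventions Classification (NIC), after CPB surgery using the Nursing Outcomes Classification (NOC"). The bullet before it already covers assessing NOC status before and after surgery, so this one adds a statement about what the interventions achieve.

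Section 3 gives the population and the approach: "we propose to assess patients who undergo CPB by means of NANDA, NIC and NOC nursing terms before and after surgery". The sequence there is diagnosis, current and hoped-for NOC, NIC, then the NOC reached.

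Section 5.4 schedules "NOC nursing taxonomy in the preoperative period, at the end of each procedure and in the postoperative period", that is, three readings. It adds: "These outcomes consist of indicators that measure the patient's health on a Likert scale (1-5").

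Section 5.1 randomises "one control group without hemofiltration (CG or 1), one group with hemofiltration using a polysulfone filter (PG or 2") and states: "The study groups will be equivalent in all aspects except the procedures they undergo".

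Section 5.7 lists two inferential routes that could bear on NOC. One is a comparison of the control group (CG) with the polysulfone group (PG). The other is within-patient: "The intrasubject change over time will be analyzed by comparing paired means using a t-test or Wilcoxon signed rank test (non-parametric variables"), taken relative to the first sample. Section 5.7 names neither NOC nor NIC.

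**The concern.** Efficacy is a causal term. To evaluate it, the trial needs patients who receive the interventions and comparable patients who do not, or some other stand-in for what would have happened without them. The protocol describes neither a concurrent group of that kind nor an external one.

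The NOC domains listed in section 3 concern fluid balance, urinary elimination, gas exchange and circulation. These are functions that a heart operation on bypass, anaesthesia and intensive care act on directly. A rise after surgery may be recovery. A fall may be the operation, and it could hide a real benefit of nursing care. A blinded, perfectly reliable rater would not change this, because the problem lies in the contrast and not in the measurement.

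At stake is one stated objective, whose reported answer could be read as evidence for or against the nursing interventions when it is neither.

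**Working it through.** **1. What each listed comparison can identify**

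Write a patient's change in NOC between two readings as

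change = S + N + F,

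where S is the effect of surgery, bypass, anaesthesia, ICU care and recovery, N is the effect of the nursing interventions, and F is the effect of the filter (zero in CG).

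- *Paired test.* In CG it estimates S + N, and in PG it estimates S + N + F. Its null is that the sum is zero, not that N is zero. If S = −0.5 and N = +0.5, the sum is 0 and a real benefit is invisible. If N = 0 and S = ±0.5, the test tends to reject although the interventions do nothing.
- *CG versus PG.* With comparable S in the two arms, the difference is F + (N in PG − N in CG). If nursing care is the same in both arms, N cancels. If it differs, for example because fluid management differs with and without a filter, the difference in N cannot be separated from F.
- *Choice of readings.* Preoperative to end of procedure includes the operation and bypass. End of procedure to postoperative leaves those out but still includes ICU care and recovery. No pair of the three readings isolates N.

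This step needs no numerical assumption.

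**2. Illustration of how strongly the paired test responds to S alone**

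*From the protocol:* about 40 patients (section 5.6), consistent with eight blocks of five (section 5.1), 8 × 5 = 40; a NOC scale of 1 to 5 (section 5.4); a paired t-test or Wilcoxon test (section 5.7). No power calculation, SD, alpha or expected shift is given, so there is no planned figure to reproduce for this objective.

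*Assumed:* two-sided 0.05; N = 0; the shift sizes; the SDs below; for the single-arm rows, an even split into 20 and 20.

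*Exact paired t-test.* With d the shift in SDs of the change score, the rejection probability is P(|T| > t₀.₉₇₅,ₙ₋₁), where T is noncentral t with n − 1 degrees of freedom and noncentrality d√n. For n = 40 and d = 0.5 the noncentrality is 0.5 × 6.32 = 3.16.

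| d | n = 40 | n = 20 (one arm) |
|---|---|---|
| 0 | 0.05 | 0.05 |
| 0.25 | 0.34 | 0.19 |
| 0.5 | 0.87 | 0.57 |
| 0.75 | 0.996 | 0.89 |
| 1.0 | 1.00 | 0.99 |

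*Simulated 1–5 scores, n = 40.* Between-patient SD 0.7, within-patient SD 0.7 per reading, scores rounded and clipped to 1–5. The latent SD of change is √(0.7² + 0.7²) = 0.99, so a 0.5-point shift is about 0.5 SD before rounding.

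| Shift (points) | Wilcoxon, upward shift from mean 3 | Wilcoxon, downward shift from mean 3.5 |
|---|---|---|
| 0 | 0.04 | 0.05 |
| 0.25 | 0.30 | 0.30 |
| 0.5 | 0.80 | 0.79 |
| 0.75 | 0.99 | 0.99 |
| 1.0 | 1.00 | 1.00 |

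The paired t-test in the upward case gives 0.30, 0.81, 0.99 and 1.00 for the four non-zero shifts. Comparing change scores between two groups of 20 that share the same shift keeps its level (0.048 to 0.054), but in this trial that comparison tests the filter.

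**The case against.** Five points can fairly be made for the protocol.

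- **No decision rule is written.** A reader might infer that the protocol commits to declaring the interventions effective if NOC rises. It does not. Section 5.7 never names NOC, and its reference to a first sample fits serial blood sampling at least as well. The paired test is reached by elimination, and the choice of test could be left to an analysis plan. This stands. However, an analysis plan can choose a test; it cannot supply a missing comparison group.
- **The intended meaning may be attainment of outcomes.** Section 3 compares the hoped-for with the achieved NOC, the glossary in Annex IV ties NOC to quality of care and outcomes achieved, and section 4.3 asks only for health status before and after surgery. NIC efficacy is not among the hypotheses in 4.2. This is a reasonable reading and it lowers the severity. It also supports the rewording, since efficacy is not the word for attainment.
- **Identical nursing care in both arms is inferred.** Section 5.1 excepts the procedures themselves, and some listed interventions concern fluid management. So it is too strong to say that the arms certainly receive the same NIC. The conclusion does not need it, because any difference would be inseparable from the filter.
- **There are three NOC readings, not two.** The later pair avoids the operation itself, but not ICU care or recovery.
- **The percentages are power against a real shift.** A reader might take the 30% to 100% as rates of falsely declaring benefit. They are not: rejections follow the sign of the assumed shift, and after a fall in NOC nobody would claim efficacy.

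**Conclusion.** The point holds as a minor one. The objective in 4.4 asks for the efficacy of the nursing interventions, and neither comparison in 5.7 can identify it under the design in 5.1. That conclusion rests on two readings of the text: that no patients without the interventions are described, and that no external comparator is named. It does not depend on the simulation.

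The size is illustrative only. With an inert intervention, 40 patients and the assumed SDs, a 0.5-point shift from other causes leads the paired test to reject about 80% of the time, in whichever direction the shift goes. The protocol gives no shift, SD or alpha, so the true figure could lie anywhere from 5% upward.

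The documents do not support the wider inference that NOC is unusable in this trial. The third hypothesis in 4.2, better health status with than without the filter, has a randomised comparator. The lactate and morbidity/mortality objectives are not affected.

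**What to change.** - **Section 4.4:** reword the last objective to describe the change in NOC scores, and the attainment of the intended NOC outcomes, before and after surgery with CPB. Drop the efficacy of the NIC as something the trial concludes.
- **Section 5.7:** add that within-patient NOC changes are descriptive, reported as mean change with 95% CI by arm, and support no statement about the effect of the nursing interventions.
- **Section 5.7:** limit NOC inference to the randomised filter versus no-filter comparison of postoperative NOC (third hypothesis in 4.2), adjusted for preoperative NOC. At present 5.7 brings in regression only if the groups turn out not to be homogeneous; here the adjustment would be fixed in advance.

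The cost is one reworded objective and two sentences. No new data or patients are needed, since preoperative NOC is already collected. The downside is giving up a claim about NIC efficacy, which this design cannot support. Keeping that claim would require a concurrent group without the interventions, which is a different trial.
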